**Methods and study design:**

A multicentre, single-blind two-armed randomized controlled trial to evaluate the effects of a 12-week (3 weeks supervised centre-based and 9 weeks home-based) individualized sensorimotor exercise program is performed. The control group stays inactive during this period. Outcomes are pain, and pain-associated function as well as motor function in adults with nonspecific low back pain. Each participant is scheduled to five measurement dates: baseline (M1), following centre-based training (M2), following home-based training (M3) and at two follow-up time points 6 months (M4) and 12 months (M5) after M1. All investigations and the assessment of the primary and secondary outcomes are performed in a standardized order: questionnaires – clinical examination – biomechanics (motor function). Subsequent statistical procedures are executed after the examination of underlying assumptions for parametric or rather non-parametric testing.

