### Participants

#### Sample size determination

A pilot feasibility study was conducted (unpublished material). The therein found outcome with the largest effect size was selected as the primary outcome for the present study. Thus, primary outcome is maximal back extension torque. Sample size calculation was based on the effect size of d = 0.24 (based on the changes in primary outcome from baseline to post-intervention (12 weeks)). For the main study, effect size was conservatively completed to d = 0.2.

Participants are allocated to intervention or control group at the ratio of 2:1. Normal distribution and variance equality are assumed. Following a determined α-error probability of 2.5 % and a β-error probability of 0.1, a minimal sample size of 1186 patients are consequently to be included into analysis (*n* = 791 in the intervention and *n* = 395 in the control group). As a dropout rate of 30 % is assumed, a total of *N* = 1542 participants are included in the study. Although motor control and stabilizing exercise are likely to show equal effects for the general population and for top athletes [15], medical access and the potential to implement medical exercise regimes into everyday life differ between these populations (e.g. training schedule, competitions). According to study aim 1, and beside the studies’ main target group, we make additional effort to also recruit a sample of athletes to gain further (beyond the main analyses) insight and test the feasibility in this much less investigated population. For dichotomization purpose, only top competitive athletes (A to D pool, participating in top level international, federal or state competitions) are further treated as athletes.

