### Statistical analysis

Data is collected and analysed centrally after assessment completion. Following visual and physiological range plausibility control, a gain score analysis (change score analysis) using the mean difference between M1 and M3 for between-group differences of the primary outcome is performed.

Hypotheses testing for all other measurement times and secondary outcomes are performed using particular fitting regressional and variance analytical testing. Potential mediators and confounders like the amount of physical activity, psychosocial scores, age, gender, initial pain level and body weight will be analysed using multiple regression mediating analyses [35] or included into variance analyses as covariates. For mediation analyses, total as well as direct and indirect effects are calculated. Sobel testing and 95 % confidence interval (CI) bias corrected bootstrapping (n_sub-samples_ = 10,000) are conducted for indirect effect quantification [36–38].

All statistical procedures are executed after the examination of underlying assumptions for parametric or rather non-parametric hypotheses testing. Due to the explorative analyses of the secondary outcomes, no alpha-error adjustment is performed. To increase statistical power, missing values are multiple imputed using standardized procedures [39] and only following (in case of psychometric scores) specific test manuals. The one-sided a priori level of significance is set at α = 0.025 for all statistical analyses.

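### The parametric or non-parametric choice is left to an inspection of the trial data even for the primary outcome, so the confirmatory hypothesis and effect measure are not fixed

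*Protocol article*

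**What the plan says.** Three parts of the protocol article bear on this.

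- **Named primary analysis.** Under Statistical analysis, "a gain score analysis (change score analysis) using the mean difference between M1 and M3 for between-group differences of the primary outcome is performed".
- **Rule for choosing the type of test.** The same section then says: "All statistical procedures are executed after the examination of underlying assumptions for parametric or rather non-parametric hypotheses testing". The abstract repeats the rule under Methods and study design: "Subsequent statistical procedures are executed after the examination of underlying assumptions for parametric or rather non-parametric testing". Neither sentence exempts the primary outcome. Neither says whether the examination is a formal test or a plot, what would count as failure, or which test would take over.
- **Basis of the sample size.** Under Sample size determination, "For the main study, effect size was conservatively completed to d = 0.2" and "Normal distribution and variance equality are assumed". The planned number is therefore the number for a comparison of two means.

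**The concern.** One sentence fixes a mean difference as the primary analysis, and a later one makes every test conditional on inspecting the data. Read together, the confirmatory analysis is a mean comparison only if the data pass a check that is not described.

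A rank comparison is not simply a safer version of the same analysis. It tests whether values in one group tend to exceed those in the other, and it agrees with the mean difference only under restrictive conditions such as a pure shift. Changing the test therefore changes the hypothesis, and the result no longer answers the question for which d = 0.2 was set.

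The plan also provides for multiple imputation. Routine pooling needs one estimate and one standard error per imputed data set, and a check applied to each set could come out differently.

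The size of the trial adds to the problem. Formal normality tests gain power with every patient, while a comparison of means relies less and less on normality. With more than a thousand patients, such a test could replace the planned analysis because of departures that do it no harm.

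**Working it through.** **1. Inputs.** Effect size d = 0.2, so SD = 1 on the standardised scale; allocation 2:1; error probabilities 2.5 % and 0.1; 791 intervention and 395 control patients, total 1186 (Sample size determination). The one-sided level of 0.025 is from Statistical analysis.

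**2. Reproducing the planned number.** For a one-sided comparison of two means with r = 2 intervention patients per control:

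n(control) = (1 + 1/r) × (z₀.₉₇₅ + z₀.₉₀)² / d² = 1.5 × (1.960 + 1.282)² / 0.04 = 1.5 × 10.507 / 0.04 = 394.03, rounded up to 395.

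The intervention group is then 2 × 395 = 790 and the total 1185, against the stated 395 + 791 = 1186. Noncentral t power at 791 and 395 is 0.9004. A two-sided 0.025 would have needed 1398. The trial is thus sized for a one-sided normal-theory comparison of means.

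**3. What a formal check would do.** The article gives no distribution, check or threshold, so all of the following is assumed: a Shapiro-Wilk test at 5 % on the pooled within-group residuals, Mann-Whitney if it rejects, and the t-test otherwise. Each scenario has 4000 simulated trials of 791 against 395, all shapes scaled to SD 1, tested one-sided at 0.025. The mixture stands for two of six sites using a different measurement mode, with equal recruitment per site and an SD ratio of 1.5.

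| Assumed shape | Shapiro-Wilk rejects (d = 0 / d = 0.2) | t-test type I error | t-test power | Two-stage type I error | Two-stage power |
|---|---|---|---|---|---|
| Normal | 5.0 % / 5.2 % | 0.0275 | 0.907 | 0.0275 | 0.906 |
| t, 10 df | 94.6 % / 93.6 % | 0.0290 | 0.896 | 0.0293 | 0.905 |
| t, 6 df | >99.9 % / >99.9 % | 0.0238 | 0.904 | 0.0228 | 0.941 |
| Gamma, skewness 0.3 | 97.6 % / 96.9 % | 0.0263 | 0.903 | 0.0270 | 0.892 |
| Gamma, skewness 0.5 | 100 % / 100 % | 0.0228 | 0.904 | 0.0245 | 0.908 |
| One third with 1.5 × SD | 70.0 % / 68.6 % | 0.0245 | 0.905 | 0.0255 | 0.910 |

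The simulation standard error is √(0.025 × 0.975 / 4000) ≈ 0.0025 for type I error and √(0.9 × 0.1 / 4000) ≈ 0.005 for power. A smaller run (300 replicates, n = 1186, rejection rate only) gave about 70 % at skewness 0.2.

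**4. Reading the table.** Under every non-normal shape the t-test keeps its level within simulation error and its power near 0.90. The formal check would nevertheless set it aside in about 70 % to 100 % of trials. The two-stage rule has type I error 0.023 to 0.029, the same range as the fixed t-test, and power 0.892 to 0.941.

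**The case against.** The strongest reply is that a primary analysis is named and the trial is sized for it. On this view the later sentence is routine wording, and how assumptions are checked belongs in a full protocol or analysis plan that is not shown. The missing threshold and replacement test are indeed no finding. But the article does state a rule, that the type of test follows from the data, and applies it to all procedures. An analysis plan could spell that rule out; it would have to depart from it to make the primary test unconditional.

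A second reply is that the Study design section has blinded evaluators perform the analyses. This lessens the risk of a choice driven by the result, although with 2:1 allocation masked groups can be recognised by their size. It does not fix the hypothesis in advance.

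Four stronger readings are tempting, and the documents do not support them:

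- **The switch is certain.** The text says only that assumptions are examined. That may be done graphically, and then the large-sample argument does not apply in this form. The shapes in the table are assumed, and the analysed variable is a within-person change, whose shape may differ from that of raw torque.
- **Pooling isokinetic and isometric sites would by itself force the switch.** Even with a formal test, an SD ratio of 1.5 gives about 70 %, and the article states no ratio.
- **Two-stage testing inflates the type I error.** The simulation shows no measurable inflation.
- **Rank methods cannot adjust for baseline or site, or give an estimate in Nm.** Stratified and covariate-adjusted rank methods exist, and the Hodges-Lehmann shift is in the units of measurement.

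**Conclusion.** The point holds as a conflict within the article. A mean-difference analysis is named and the sample size rests on it, yet a general rule lets the data decide whether it is used. The consequence is a confirmatory hypothesis and effect measure that are not settled before the data are seen. No loss of type I error control has been shown.

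How often the analysis would change depends on a check that the article does not describe. With a 5 % Shapiro-Wilk test at 1186 patients it would be about 70 % of trials at skewness 0.2 or with the one-third mixture at SD ratio 1.5, and about 95 % or more at skewness 0.3. These figures rest on assumed shapes and an assumed test. They show that such a check is a poor guide at this sample size, and do not predict what will happen in this trial.

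**What to change.** Add one sentence to Statistical analysis: the primary outcome is analysed by the between-group mean difference in M1 to M3 change, whatever the assumption checks show, with heteroscedasticity-robust standard errors or a bootstrap confidence interval. Limit the parametric or non-parametric choice to the other analyses, use the checks on the primary outcome for description, and name one rank-based analysis as a sensitivity analysis.

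Preferably, estimate the mean difference in a linear model adjusted for the M1 value and study site, both of which are already collected. This is an improvement on top of the fix; the unadjusted gain score comparison, fixed in advance, would also resolve the conflict.

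The cost is one sentence. The sample size stays at 1186 with power 0.9004. The price is some power if tails are heavy: with t on 6 df the two-stage rule reached 0.941 against 0.904 for the fixed t-test, a difference of 0.037. The fixed test still delivers the planned 90 %.

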## Discussion

Primary aim of the study is to test the feasibility and efficacy of individualized sensorimotor training interventions for the treatment of nonspecific low back pain. To do so, a standardized and practically relevant diagnostic assessment and a randomized controlled single-blind intervention design is used.

The intervention consists of sensorimotor exercises for core/trunk stability with additive perturbation elements [40] in highly individualized yet guided group therapy sessions. Although there is compelling evidence for the relevance of exercise elements in the therapy of chronic nonspecific low back pain [11, 14], only limited data provides solid information on dose-response and sensorimotor training individualization. Moreover, the biopsychosocial effects of such interventions are yet to be unravelled.

A strength of the intervention implemented is the symbiosis of the hypothesized large and clinically relevant effect and the short exercise duration as well as the low use of resources for both the home- and centre-based intervention [11], making it a cost-effective intervention. The individualized diagnostics and exercises are of further value. The heterogeneity of the study population may become a limitation for data interpretation and practical relevance deduction however. To avoid or minimize this potential bias, mediation analyses, multiple regressions and analyses including potential co-variables are performed. Together with the randomized study design and the resulting respect of unknown confounders, considering these known and suggested confounders provides a sufficient statistical power. A common limitation in exercise trials is the limited possibility to blind the participants. This limitation is increased by the subjective assessment of pain and pain-related function. To reduce the risk of bias as much as possible, all investigators are blinded to intervention allocation.

A suggested underlying mechanism for the hypothesised effect is mostly seen in the analgesic effect of exercise. Exercise releases beta-endorphin both spinal and supraspinal by activating μ-opioid receptors [41]. Following that, an acute sensible decrease in pain is felt. On the long term, exercise and, in particular, sensorimotor or motor control training increases the functional capacity of all involved tissues [42].

Our study provides further evidence for the efficacy or non-efficacy of motor control exercise targeting neuromuscular factors like kinematics, strength, postural control and pain [11]. Beyond that, the results and practical relevance of our study will be of importance not only for researchers and policy makers but also for patients suffering from nonspecific low back pain. On the one hand, the target group diagnostics we implement are of relevance for the planning and longitudinal screening of our individualized motor control exercise. On the other hand and if of clinical relevance, our motor control exercise provides a as far as possible individualized intervention, characterized by low effort and cost.

### Trial status

Participant recruiting started January 2016. At the time of manuscript submission, we had included 142 participants into the study with no participant having completed the intervention. Screening completion is anticipated to be April 2017, measurement completion April 2018 and study completion is expected to be December 2018.

## Abbreviations

AEQ-PPS: Avoidance‐Endurance Questionnaire
BSSS: Berlin Social Support Scales
CI: confidence interval
CMJ: counter movement
CoP: center of pressure; static balance
COP: centre of pressure
CPG: Chronic Pain Grade Questionnaire
CRT: Chair Rise Test
DRKS: German Clinical Trials Register
F: force/strength
FABQ: Fear-Avoidance Belief Questionnaire
HADS: Hospital Anxiety and Depression Scale
ICC: intraclass correlation coefficient
IPAQ: International Physical Activity Questionnaires
LE: life events
M1: M2, M3, M4, M5, visits 1–5
MiSpEx: Medicine in Spine Exercise
MIVF: maximal isometric voluntary force
N: number
NRS: numeric rating scale
ROM: range of motion/kinematic analyses
RQ-2: relationship questionnaire
SES: socio-economic status
SMT: sensorimotor training
TICS: Trier Inventory for Chronic Stress
TuG: Timed Up and Go Test
